### Statistical analysis

#### Sample size

The sample size was calculated based on results reported by Boggio et al. [12]. Boggio et al. [12] administered active or sham tDCS once daily for 5 days to patients with Alzheimer’s dementia and compared their performance for visual recognition tasks before and at 1 month after treatment. Based on differences in mean correct response rate (ε = 11.61, σ_d_ = 11.62; 1:1 allocation ratio per group) in the previous study, a sample size was estimated to obtain at least 90% power (1 − beta = 0.9) to detect a treatment difference of 11.61 (SD 11.62 of change) in visual recognition task scores at a significance level of 0.05 (α = 0.05). A total of 14 persons (seven per sequence) were selected by PASS 12 (NCSS, LLC, Kaysville, Utah, USA, https://www.ncss.com/) as the smallest sample size. This study targeted a total of 20 subjects (10 per group) considering a drop rate of 30%.

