### Outcome measures

#### Primary outcomes

This study will determine cognitive improvement by using visual recognition tasks similar to those described previously [12, 13] in which tDCS is administered to patients with Alzheimer’s dementia. In the encoding phase, screens with two, four, six, and eight stimulations are displayed for 10 s, respectively. Participants are required to memorize pictures displayed on each screen. After a 1-s interval, the test phase is started and the specific stimulus is displayed. Participants are required to respond as rapidly as possible whether or not the stimulus involves the picture seen in the encoding phase. Similar to previous studies, our task comprises an encoding phase and a test phase. In contrast to previous studies, black-and-white icon stimuli will be used to provide a more intuitive and simple format. Objects, human body parts, and animals that are generally seen in daily life will be used. The test phase will comprise three, six, eight, and ten test trials of two, four, six, and eight pictures, respectively, in the encoding phase.

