#### Statistical methods

For primary efficacy assessment, differences in correct response rate in the visual recognition task before and after treatment will be calculated. Differences between active and sham setups will be analyzed by a general linear model [37] to assess major (treatment), period (time), and carry-over effects. For secondary efficacy assessment, analysis of variance (ANOVA) of changes in each sub-item of CERAD-K will be conducted. Only the results of the participants who completed the intervention will be included in these efficacy analyses, but the side effects will be reported for all participants.

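### The 90% power at 14 completers holds only if 11.62 is the SD of the active-minus-sham difference in change, which the protocol neither states clearly nor justifies for its 27-trial task

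*Protocol article*

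**What the plan says.** The Sample size section takes its effect and SD from an earlier study in Alzheimer's dementia that "compared their performance for visual recognition tasks before and at 1 month after treatment". It gives the inputs as "ε = 11.61, σ_d_ = 11.62; 1:1 allocation ratio per group) in the previous study", then restates the target as "to detect a treatment difference of 11.61 (SD 11.62 of change) in visual recognition task scores at a significance level of 0.05". From these it derives 14 completers (seven per sequence) for at least 90% power, and 20 enrolled to allow for 30% dropout.

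Under Statistical methods, the primary measure is a change: "differences in correct response rate in the visual recognition task before and after treatment will be calculated". Active and sham are then compared in a general linear model with treatment, period and carry-over effects, in participants who completed the intervention. Table 1 places the task at T1 and T2 (first period) and at T3 and T4 (second period).

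Under Primary outcomes the task is fixed: "The test phase will comprise three, six, eight, and ten test trials of two, four, six, and eight pictures, respectively, in the encoding phase". That is 3 + 6 + 8 + 10 = 27 yes/no trials per assessment, with no repeats mentioned. The section also says that the task differs from the earlier ones in its stimuli.

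**The concern.** The primary contrast is a difference of two changes, so it uses four scores per person. The power calculation needs the SD of that quantity. The symbol σ_d suggests that 11.62 is this SD, but the phrase about the SD of change, next to a source described as a before-after comparison, allows it to be the SD of one change. The two differ by a factor that depends on the correlation between a person's two changes, and the protocol gives no such correlation.

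The task raises the same doubt by another route. A score out of 27 carries appreciable scoring noise, and a contrast of four such scores carries more.

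At stake is how a null result is read. With 90% power it is fair evidence against an effect of about one SD. With 65% to 80% power, the trial had a sizeable chance of missing that effect.

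**Working it through.** **Inputs.** From Sample size: difference 11.61 points, SD 11.62, α = 0.05 (two-sided reproduces the plan), power 90%, 14 completers, 20 enrolled. From Primary outcomes: 27 trials per score. From Statistical methods and Table 1: contrast = (T2 − T1) against (T4 − T3), active minus sham. Correlation r and baseline accuracy p are assumptions, because the document gives neither.

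**1. The plan's own figure.** 2×2 cross-over t test, noncentral t with df = N − 2 and noncentrality 11.61 / (SD/√N). With SD = 11.62:
- N = 12: 87.6%
- N = 14: 92.9%
- N = 20: 98.8%

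So 14 is the smallest even N that reaches 90%, and 14 / 0.70 = 20. Both figures reproduce, with 11.62 as the SD of the active-minus-sham difference in change.

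**2. If 11.62 is the SD of one within-period change.** The contrast then has SD = 11.62 × √(2(1 − r)).

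| r | contrast SD | power, N = 14 | power, N = 20 | N for 90% |
|---|---|---|---|---|
| 0 | 16.43 | 68.0% | 84.8% | 24 |
| 0.25 | 14.23 | 80.0% | 93.2% | 18 |
| 0.4 | 12.73 | 87.9% | 97.1% | 16 |
| 0.5 | 11.62 | 92.9% | 98.8% | 14 |

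Power at 14 passes 90% at r of about 0.45 (SD 12.19, 90.5%). For orientation: if the four scores have equal variance and equal pairwise correlation c, the covariance of the two changes is c − c − c + c = 0, so r = 0. A positive r needs people who gain consistently in both periods, for example through practice.

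**3. Scoring noise alone.** Assume independent trials, equal item difficulty and no real session-to-session variation. Three scores have accuracy p and the post-active score has q = p + 0.1161. The contrast SD in points is 100 × √[(3p(1 − p) + q(1 − q)) / 27].

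Example, p = 0.70, q = 0.8161: (3 × 0.21 + 0.1501) / 27 = 0.02889; the square root is 0.170, so SD = 17.0.

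| baseline accuracy p | SD | power, N = 14 | power, N = 20 |
|---|---|---|---|
| 60% | 18.5 | 57.9% | 75.7% |
| 70% | 17.0 | 65.1% | 82.3% |
| 80% | 14.4 | 79.3% | 92.7% |
| 85% | 12.4 | 89.5% | 97.7% |
| 87% | 11.4 | 93.6% | 99.0% |

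Under these assumptions the noise falls to 11.62 only near 87%. The ceiling for a mean gain of 11.61 is 100 − 11.61 = 88.39%.

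**4. Unequal difficulty.** If accuracy falls as the number of pictures rises, the noise shrinks. Five assumed profiles with mean accuracy of 75% to 83% give SDs of 12.2 to 15.2 and power of 74% to 91% at 14. For example, 100/95/85/70% across the four set sizes gives 12.55 and 88.8%.

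**5. What baseline adjustment would do.** In simulation under the assumptions of step 3 with N = 14, I regressed the active-minus-sham difference in post-treatment scores on sequence and the difference in period baselines (df = 11), in place of the raw difference in changes (df = 12). Power rose from about 65% to 90% at p = 70%, and from about 80% to 98% at p = 80%. This is a favourable case, because there the baseline difference is pure noise. The gain is smaller where baselines predict post-treatment differences within a person.

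**The case against.** Nothing in the sample size arithmetic is wrong. σ_d is the usual symbol for the SD of paired differences. The phrase about change follows directly on the treatment difference, so it can mean the SD of that difference for a change-score endpoint, and this reading returns the stated N. Which SD the cited study reported cannot be settled from this document. All of that stands: the label is ambiguous, not shown to be misused.

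A reader might infer that true power at 14 is 60% to 80%, or that a 27-trial task cannot yield an SD of 11.62. The document supports neither. The first needs an r near zero or an accuracy of about 60% to 80%, and neither is given. The second is too strong, since with accuracy near 85%, or with some unequal-difficulty profiles, the noise SD is about 12 to 12.5 and power about 89% to 91%. The task has unequal difficulty by design.

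Fourteen is also the planned low case; fewer dropouts mean more power. The Discussion names small scale as a limitation and calls for a larger study to validate the effect. This lowers the severity. But the section claims at least 90% power at 14, the efficacy analysis uses completers only, and 30% dropout is planned for, so 14 is the right number to examine. Step 3 includes no real session-to-session variation, which would add to the SD.

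**Conclusion.** The point holds as a doubt about a power assumption, not as an arithmetic error. The 90% claim rests on an SD that the text does not identify clearly and does not justify for a difference of two changes on this task.

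- If 11.62 is the SD of one change: power at 14 is about 68% (r = 0) to 80% (r = 0.25), and 90% or more from r of about 0.45. With 20 completers it is 85% to 93% for r from 0 to 0.25.
- Whichever SD was meant: at assumed baseline accuracy of 60% to 80%, independent-trial noise alone takes the contrast SD to 18.5 to 14.4, and power at 14 to 58% to 79%. Near 85% accuracy the shortfall almost vanishes.

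A shortfall is therefore plausible and could be sizeable, but it is not proven. Severity is moderate.

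**What to change.** 1. **Statistical methods.** In the general linear model, analyse each period's post-treatment correct response rate with that period's baseline (T1 or T3) as covariate, in place of raw change scores. Equivalently, analyse the active-minus-sham difference in post-treatment scores adjusted for the difference in period baselines. Both baselines are already collected. The cost is one degree of freedom.
2. **Sample size.** State which SD 11.62 is and why it suits this 27-trial task. Give power as conditional, for example: about 93% at 14 completers if 11.62 is the SD of the active-minus-sham difference in change; if it is the SD of one change, 68% to 80% at 14 and 85% to 93% at 20 for a correlation of 0 to 0.25. Add the range over assumed baseline accuracy.

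No extra patients or visits are needed. The price is a less favourable power statement. The change of analysis should be fixed before unblinding.

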#### Statistical methods

For primary efficacy assessment, differences in correct response rate in the visual recognition task before and after treatment will be calculated. Differences between active and sham setups will be analyzed by a general linear model [37] to assess major (treatment), period (time), and carry-over effects. For secondary efficacy assessment, analysis of variance (ANOVA) of changes in each sub-item of CERAD-K will be conducted. Only the results of the participants who completed the intervention will be included in these efficacy analyses, but the side effects will be reported for all participants.

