#### Randomization and blinding

A random group assignment list was created by statisticians who are not involved in data collection using PASS 12 (NCSS, LLC, Kaysville, Utah, USA, https://www.ncss.com/). Participants are allocated 1:1 to the active first group and sham first group. The device manager will set up the device according to the assignment list in order of participant’s registration number. The same single device can be set to sham or active status using the administration menu. Because only the device manager, who will not contact the participants, knows the assignment list and the password required to access the administration menu, other investigators and participants will remain blind to it. This masks investigators and enables the use of fewer devices.

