#### Study schedule

Assessments at each visit are listed in Table 1 & Fig. 3. Details of each phase are as follows:Screening phase: Only participants with written consent will be screened. Subjects who meet the inclusion criteria will be randomized.Treatment phase I (visit 1 to visit 2): During visit 1 (T1), a visual recognition task and a neuropsychological test will be conducted with baseline data for efficacy assessment. After the outcome measures are taken, including covariance measurements, training for tDCS use will be conducted for subjects or their caregivers by using a tDCS device for practice and a check list. The first clinical device application and assessment of side effects will be conducted for subjects who have passed the test for tDCS use. Starting from the day after the first visit, the subject (or his/her caregiver) will use the device once daily for 2 weeks (a total of 14 days). It is recommended to use the device at specific times (e.g., immediately after face washing in the morning). Information about time and period of application by the subject are automatically saved in the device. Researchers will monitor the information remotely at certain times of the day and will call if tDCS is not applied.Wash-out phase (visit 2 to visit 3): The subject will be required to visit the hospital 2 weeks after visit T1 for efficacy assessment. Subsequently, appropriate use of the device by subjects will be assessed by the investigator using a tDCS device for practice. A log of the returned device will be printed by the device manager for records so that blinding is maintained. Later, a 2-week wash-out phase will be conducted.Treatment phase II (visit 3 to visit 4): The subject will be required to visit the hospital at 4 weeks after visit T1. Similar to treatment I, training sessions will be conducted and proficiency with the device will be assessed. Also similar to treatment 1, the device will be used at home after returning from the hospital. After returning home, subjects will apply the device once daily for 2 weeks (14 days).Follow-up phase: Subjects will be asked to visit the study institution at 6 weeks after visit T1. Appropriateness of device application and efficacy assessment will be evaluated by the investigator. Finally, a follow-up assessment will be conducted during a study visit at 2 weeks after the last treatment visit (T4).

**Table 1 Tab1:** List of tests conducted at each visit

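### The efficacy analyses keep only participants who complete the intervention, with about 6 of 20 allowed for as losses, so the primary result is selected on a post-randomisation event and collected data are discarded

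*Protocol article*

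**What the plan says.** The Statistical methods section describes a general linear model for the change in correct response rate (treatment, period and carry-over) and an ANOVA for the CERAD-K sub-items. It then limits both: "Only the results of the participants who completed the intervention will be included in these efficacy analyses". The same sentence reports side effects for everyone, so the restriction is deliberate and specific to efficacy. The article does not say what counts as completing.

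The Sample size section allows for substantial loss: "This study targeted a total of 20 subjects (10 per group) considering a drop rate of 30"%. The Study schedule places randomisation at the end of screening ("Subjects who meet the inclusion criteria will be randomized"). Device training, the device test and the two 14-day home courses all come later. Table 1 schedules the visual recognition task at T1, T2, T3, T4 and F1.

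The Discussion adds two relevant admissions: the burden of learning the device may affect compliance in people with cognitive decline, and the two-week wash-out may be too short.

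**The concern.** Whether a person completes is known only after randomisation. It can depend on how well they tolerate the stimulation, whether they feel a benefit, and how well they cope with a daily home procedure. An analysis restricted to completers therefore estimates the effect in a self-selected group. The trial asks whether patients with MCI can treat themselves at home and benefit, and those for whom home use failed are the ones removed.

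The rule also discards information. Someone who leaves after T2 has a complete, randomised period I change, and period I is the comparison that carry-over cannot reach. This matters here because the protocol doubts its own wash-out. If completing means doing every session, people who attended all visits but missed some sessions would be lost as well. As the term is undefined, that choice could be made after the data are seen.

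**Working it through.** **Inputs, all from the protocol**
- Planned effect and SD: "to detect a treatment difference of 11.61 (SD 11.62 of change) in visual recognition task scores".
- Power: "at least 90% power (1 − beta = 0.9").
- Alpha: "at a significance level of 0.05 (α = 0.05"). Sidedness is not stated; two-sided is assumed.
- Evaluable number: "A total of 14 persons (seven per sequence) were selected by PASS 12".
- Allocation: "Participants are allocated 1:1 to the active first group and sham first group".
- Target of 20, with 30% loss.

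**1. Reproducing the plan's figures.** For a 2×2 cross-over, SE = SD/√N with N − 2 degrees of freedom.
- N = 14: SE = 11.62/√14 = 3.11; the noncentral t distribution gives power 0.929.
- N = 13 gives 0.906, and equal sequences round this up to 14.
- Inflation for loss: 14/(1 − 0.30) = 20.

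Both stated numbers reproduce.

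**2. Size of the exclusion.** 0.30 × 20 = 6, leaving 14 of 20 (70%) in the efficacy analyses if loss runs as planned.

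**3. Power under the completer rule.** It stays at 0.929 with a 7/7 split. With uneven loss at N = 14, using SE = (11.62/2) × √(1/a + 1/b):

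| Completers per sequence | Power |
|---|---|
| 7/7 | 0.929 |
| 8/6 | 0.924 |
| 9/5 | 0.907 |
| 10/4 | 0.872 |

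Only the most uneven of these splits falls below 90%.

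**4. Illustration of selection.** Assume that the 14 completers have the planned effect of 11.61 and the six others have an effect x. The mean over all randomised is (14 × 11.61 + 6x)/20.
- x = 0: 162.54/20 = 8.13; 11.61/8.13 = 1.43, so the completer figure is 43% (3.5 points) higher.
- x = 5.805 (half): (162.54 + 34.83)/20 = 9.87; 11.61/9.87 = 1.18, so it is 18% (1.7 points) higher.
- x = 11.61: no difference.

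The values of x are assumptions; the protocol gives none.

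**5. Information in period I.** Suppose that all six leavers have a T1-to-T2 change, three per sequence. Let ρ be the correlation between a person's two period changes. The SD of one change is 11.62/√(2(1 − ρ)), and a 3 v 3 contrast has SE = SD × √(2/3). Pooling by inverse variance with the completers' SE of 3.11:
- ρ = 0: SD 8.22, contrast SE 6.71; pooled SE = 1/√(1/3.11² + 1/6.71²) = 2.82.
- ρ = 0.5: SD 11.62, contrast SE 9.49; pooled SE = 2.95.

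The gain is about 5% to 9% of the standard error. Both figures assume no carry-over.

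**The case against.** The best defence is that this is a small cross-over study that the protocol itself presents as exploratory. Each completer receives both conditions, so the comparison is within the same people and is not ordinary differential dropout between arms. Someone without period II supplies no within-patient contrast, so part of the exclusion follows from the design. Enrolling 20 already covers the expected loss. All of this stands. It does not remove selection of people who tolerate or respond to the treatment, and it does not justify dropping usable period I data. An unseen analysis plan may add further analysis sets, but the article fixes this one explicitly.

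Several stronger readings are tempting but unsupported:
- *Six is a maximum, or a forecast.* The 30% is a planning allowance; actual loss may be smaller or larger.
- *The completer result is biased by 43%.* That needs non-completers to gain exactly nothing. A mixed model would not return 8.1 either, because it does not score leavers as zero.
- *Power would rise to 0.988 with all 20.* That needs complete data and the full effect in everyone. Under the dilution in step 4, power with 20 complete participants is about 0.84 to 0.95.
- *People who missed sessions are certainly excluded.* This is one reading of an undefined term.
- *Ability to use the device differs by arm.* The same device serves both conditions, training is without stimulation, and a caregiver may help.
- *Randomising before the device test biases the comparison.* A blinded failure before any stimulation cannot depend on allocation. It wastes allocations and may unbalance the sequences.

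**Conclusion.** The concern holds as a problem of selection and lost information, not of power. The protocol explicitly conditions its primary and secondary efficacy results on a post-randomisation event that it links to patient characteristics, and it allows for about 6 of 20 participants being lost. That completion differs between active and sham is a reasoned risk, not something the document shows.

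The size of any distortion cannot be derived from the protocol. The 18% to 43% range rests wholly on assuming that non-completers gain between none and half of the planned effect. The reduction in standard error, from 3.11 to about 2.8 to 2.95, assumes that all six leavers supply period I data, split 3 v 3, with a correlation between period changes of 0 to 0.5. The conclusion depends on neither illustration: the rule decides who counts in the primary result, and a better analysis can be run on data already scheduled for collection.

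**What to change.** Before unblinding, amend the Statistical methods section as follows:
- Make the primary analysis a mixed model with a random subject effect and fixed treatment and period effects. Include all randomised participants with at least one post-treatment score, analysed as randomised whatever the number of sessions done.
- Continue to assess carry-over as planned.
- Define what completing the intervention means, and report the completer analysis as a sensitivity analysis.
- Report, by sequence, the randomised participants with no post-treatment score, since requiring one score is itself a post-randomisation condition.

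This costs analysis work and a wording change, with no extra visits or participants. The estimate may be somewhat smaller because participants with low adherence count, and the use of leavers' period I data rests on a missing-at-random assumption. Moving allocation to after the T1 device test is not needed for this point, and could not help those already randomised in a trial that has recruited since March 2018.

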## Discussion

Despite promising results reported by studies investigating cognitive improvement using non-invasive brain stimulation methods, their actual use in clinical practice is still limited. Reasons restricting their clinical use may include: 1) the long-term effect cannot be confirmed as most previous studies only monitored changes after single and temporal treatment; 2) although the effect of > 2-week repetitive application was observed in several studies, patients were asked to visit hospital every day in order to reproduce such effects in actual practice. In this study, patients will be asked to use miniaturized, automated tDCS that is available for self-administration at home under remote surveillance. If the elderly with cognitive decline can use tDCS at home, patients with diverse diseases without cognitive impairment can use tDCS safely as well. Our findings may suggest that home-based tDCS is a practical treatment for patients, thus addressing limitations of non-invasive brain stimulation methods described previously.

Previous results have indicated a high incidence of dementia in elderly patients with MCI compared to the general elderly population. According to Petersen et al. [1, 3], approximately 10–15% of the aging population progresses to Alzheimer’s disease while 80% of elderly with MCI present symptoms of dementia after 6 years. However, drug therapies that delay progress from MCI to dementia or improve cognitive function are unknown [38]. Considering that the elderly are generally vulnerable to side effects of drugs and drug–drug interactions due to polypharmacy, non-drug therapies are in demand. The potential of tDCS to significantly improve cognitive function in MCI provides a significant treatment alternative for not only patients with MCI, but also those with early-stage Alzheimer’s dementia. In addition, improving cognitive function is expected to help reduce social care burdens and improve patients’ subjective quality of life by maintaining their independence.

Cognitive function consists of various interacting domains, with specific domains influenced greatly by disease or therapy. This study seeks to use visual recognition tasks as well as standardized comprehensive neuropsychological assessments and symptom questionnaires for efficacy assessment. Therefore, it is expected to unravel complex patterns of change in cognition and symptoms related to the use of tDCS. In addition, it may facilitate the assessment of neuropsychological characteristics of patients with significant response to tDCS.

Lastly, applications and technologies for symptom and side effect assessment as well as remote support that are integrated into the smart phone in this study are applicable not only to tDCS studies, but also to other clinical trials. Such home-based clinical trial systems utilizing established technologies are inexpensive to install. They are highly expandable due to compatibility with a wide range of devices and applications. These methodologies are relevant to elderly patients facing difficulty with hospital visits. They are also useful for clinical studies investigating the effect of physical activity using ambulatory monitoring devices.

This study has some limitations. First, the study is a small-scale cross-over study. Although cross-over design enables exploratory studies in a relatively small number of patients, a large-scale study is needed to validate the clinical effect. Second, a 2-week wash-out period in this study might be insufficient given that studies demonstrating a consistent effect with tDCS are still unavailable. The effect of tDCS has been reported to continue in patients with Alzheimer’s disease [12]. To overcome this limitation, we will analyze the carry-over effect using a general linear model. Third, psychological factors in the elderly associated with the use of a smart phone may influence this study. The elderly who experience cognitive decline may feel burdened by having to learn how to use the new devices. This can influence their compliance with the study protocol. The interface and devices should be optimized for use in the elderly population and verified in further studies.

In summary, this study will facilitate the application of tDCS in MCI as a home-based, self-administered intervention and a realistic therapy. Furthermore, confirmation of tDCS as a significant therapeutic method will facilitate treatment for Alzheimer’s dementia at an early stage, including MCI (Additional file 1).

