### Design and procedure

#### Trial design

This study was designed as a 9-week, multicenter, randomized, double-blinded, cross-over clinical study. All subjects will undergo a 2-week treatment phase twice (treatment I and treatment II) with a 2-week washout period. A follow-up assessment will be conducted 2 weeks after completion of the second treatment phase (treatment II; Fig. 2). In treatment I, either active or sham tDCS will be administered. In treatment II, tDCS under different conditions will be administered.

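### A carry-over term in the general linear model cannot overcome a short washout in this two-period cross-over: it leaves the treatment estimate uncorrected or reduces it to Treatment I, without the stated 90% power

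*Protocol article*

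**What the plan says.** Trial design: "All subjects will undergo a 2-week treatment phase twice (treatment I and treatment II) with a 2-week washout period". Table 1 puts T1 on day 1, T2 on day 14, T3 on day 28 and T4 on day 42, with the visual recognition task at each.

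Statistical methods: the primary variable is the before-to-after change in correct response rate. Active and sham are to be "analyzed by a general linear model [37] to assess major (treatment), period (time), and carry-over effects".

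Sample size: the inputs ("ε = 11.61, σ_d_ = 11.62; 1:1 allocation ratio per group") come from a study of Alzheimer's dementia that "compared their performance for visual recognition tasks before and at 1 month after treatment". The result: "A total of 14 persons (seven per sequence) were selected by PASS 12", raised to 20 for 30% dropout. No allowance is made for adjusting treatment for carry-over.

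Discussion, limitations: two weeks of washout might not be enough, and the effect has been reported to last, citing the same study that supplied the sample size. The next sentence is "To overcome this limitation, we will analyze the carry-over effect using a general linear model".

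**The concern.** The protocol appears to plan on an effect seen a month after treatment, allows two weeks for it to clear, and relies on the analysis to deal with what is left. In a two-sequence, two-period trial the data do not allow that. Carry-over from active to sham is aliased with sequence, and equally with a treatment effect that differs between periods. A carry-over term can therefore do one of two things:

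- It can be tested as a between-sequence effect. The active-sham estimate is then unchanged, whatever the test shows.
- It can be fitted alongside treatment. The estimate then rests on Treatment I alone, a parallel-group comparison for which the trial was not sized.

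At stake is the primary estimate of a 20-person trial, and whether readers take it to be free of carry-over because the protocol says so.

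**Working it through.** **Inputs.** Difference 11.61, SD 11.62 (call it σ_d, the SD of the within-person active-sham contrast), 14 evaluable, 20 enrolled, alpha 0.05, all from Sample size; visit days from Table 1. Sidedness is not stated; two-sided reproduces the plan's figure. The correlation r between a participant's two period changes is not given, so I show -0.2, 0 and 0.5 as assumptions.

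**1. The plan's own figure.** Two-sided t-test for a 2x2 cross-over, noncentrality 11.61/(11.62/√N), df N - 2.
- N = 14: noncentrality 3.74, power 0.929.
- N = 12: power 0.876.

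So 14 is the smallest balanced total, and 14/0.7 = 20. Both figures reproduce, for a model without carry-over.

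**2. Aliasing.** With 14 participant effects plus period, treatment and carry-over, the design matrix has 17 columns and rank 16. Without carry-over the rank is also 16, so carry-over adds nothing that can be estimated within participants. With participants as random effects carry-over can be fitted, but the generalised least squares estimate of treatment then equals the Treatment I between-group difference (checked numerically).

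**3. If carry-over is only tested.** The test compares the sum of the two period changes between sequences. SD of the sum = σ_d·√((1+r)/(1-r)), which is 11.62 at r = 0 and 20.13 at r = 0.5. Power with 7 per sequence:

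| Size of the contrast | r = 0 | r = 0.5 |
|---|---|---|
| 11.61 (the full effect) | 0.41 | 0.17 |
| 5.8 (half of it) | 0.14 | 0.08 |

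A non-significant result would say little, and a significant one would leave the treatment estimate as it was.

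**4. If carry-over is fitted.** SD of one period's change = σ_d/√(2(1-r)); noncentrality = 11.61/(SD·√(2/n)) with n per sequence. Power of the Treatment I comparison:

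| r | SD of change | 14 completers | 20 completers |
|---|---|---|---|
| -0.2 | 7.50 | 0.76 | 0.91 |
| 0 | 8.22 | 0.68 | 0.85 |
| 0.5 | 11.62 | 0.41 | 0.56 |

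Without the term, power is 0.93 with 14 and 0.99 with 20. With 14 completers no row reaches 90%; with 20, only r = -0.2 does.

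**5. Bias of the change-score estimate without adjustment.** Let τ be the treatment effect, and c3 and c4 the residual active effect at T3 and T4 in active-first participants. Their Treatment II change contains c4 - c3. Averaging the active-sham contrast over the sequences gives

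½[τ - (c4 - c3)] + ½τ + ½[0] with period effects cancelling, that is, τ + (c3 - c4)/2.

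- c3 = c4: bias 0, estimate 11.61.
- Half the effect left at T3, none at T4: 11.61 + 5.805/2 = 14.5.

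The sum contrast in step 3 estimates c4 - c3, so it tracks this bias. It is silent when the residual is constant, but then the estimate is unbiased.

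**6. Timing.** T3 is 28 - 14 = 14 days after T2, and T4 is 42 - 14 = 28 days after it. An effect that persists for a month would be present at both visits.

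**The case against.** **The limitation is disclosed.** The Discussion admits that the washout may be short, describes the design as suited to exploratory work and calls for a larger trial. That stands, and it lowers the severity. The sentence that follows still says the analysis overcomes the problem, which is wrong as written. An unseen analysis plan could specify the model, but it could not make carry-over separable in this design.

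**The change score already protects the estimate.** This stands for a constant residual: each period has its own baseline, so it cancels. It does not stand for a residual that fades between T3 and T4. The protocol does not make this argument.

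**The power loss may be modest.** This stands in part. Equal correlation across T1 to T4 implies r = 0 for the two changes, and serially decaying correlation implies a negative r. The text speaks only of assessing carry-over, so joint fitting is one reading.

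Three stronger conclusions might be inferred, and the documents do not support them:
- *That the estimate is inflated by half.* A figure of 17.4 (11.61 + 11.61/2) needs the full effect at T3 and none at T4. That conflicts with persistence for a month, under which the bias is about zero.
- *That most of the power is lost.* That needs carry-over to be fitted, r of about 0.4 or more, and only 14 completers.
- *That a carry-over test will choose the final analysis.* Nothing in the text describes such a two-stage procedure.

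**Conclusion.** The point holds as a should-fix. The claim that a general linear model overcomes an insufficient washout is wrong for this design under either reading of the carry-over term. If carry-over is tested, nothing is corrected and the test has low power. If it is fitted, power with 14 completers is 0.76 to 0.41 rather than 0.93, over an assumed r of -0.2 to 0.5. Bias in the planned change-score estimate runs from zero (constant residual) upward in favour of active (fading residual); 14.5 against 11.61 is an illustration, not a forecast.

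This rests on additive effects, no residual effect of sham, 11.62 being the SD of the within-person contrast (the reading that reproduces 14), and assumed values of r. That 11.61 is the 1-month difference is the natural reading of Sample size, but it is not stated outright.

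**What to change.** - **Primary model.** State it as participant + period + treatment on the period change scores, with no carry-over term and no preliminary carry-over test. This is the analysis that the sample size of 14 supports.
- **Carry-over, descriptively.** Report two between-sequence differences with 95% confidence intervals: T3 minus T1, which estimates the residual effect at T3; and the sum of the two period changes, which tracks c3 - c4 and hence the bias. The first alone is not a measure of bias, since it would be large under constant persistence, where the estimate is unbiased.
- **Sensitivity analysis.** Report the Treatment I comparison (T2 adjusted for T1), which is free of carry-over. It should not be a condition for a positive conclusion, because it is underpowered over most of the range shown.
- **Wording.** In the Discussion, replace the claim to overcome the limitation with a statement that the analysis cannot remove carry-over in this design.
- **Reconciliation.** The sponsor should reconcile the 2-week washout with the 1-month comparison from which the planning effect appears to come.

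The cost is statistical wording before unblinding; all the data needed are already scheduled in Table 1. The downside is that the report must admit that carry-over is not removed.
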